**Figure 4 figure4:**
[figure not shown]
(A) Dot Memory Test landing page, (B) instructions, (C) E’s and F’s distraction phase, and (D) response page.

The ActiGraph produces variables representing different facets of day and nighttime physical activity. Our main measurements for daytime (awake) activity are activity counts, steps, physical activity intensity, and sedentary bouts across the 14-day home monitoring period, providing daily and typical activity levels. Our main measures for nighttime activity will be sleep latency, total sleep time, wake after sleep onset, and sleep efficiency.

### Examiner Certification Process

To ensure standard test protocol administration across study sites and time, a rigorous examiner certification process was established. To achieve initial certification to administer tests, research staff were required to read the study protocol and manual of procedures, read the NIHTB Administration Manual, watch all training videos, and pass quizzes at the end of each training video. Training videos were from the NIH Toolbox eLearning Course or were custom-made by the study investigators, who had expertise in motor testing ([name]) or neuropsychological test administration ([name], [name], and [name]). The videos provide detailed instructions on general best practices for test administration and how to administer each non-NIHTB test. After these initial training activities, research staff practiced the full laboratory-visit protocol with at least 5 nonparticipants (eg, fellow laboratory staff), video recording the final testing session. This video along with all accompanying case report forms and test materials were evaluated by 2 investigators—one with expertise in administering motor tests and one with expertise in administering neuropsychological tests. Together, the evaluators decided whether the examiner passed or failed the certification. Failure is defined as 2 or more minor errors or 1 or more major errors. A major error is defined as any error that indicates a lack of understanding of the proper standardized administration of any test or any scoring error that is large enough to change the interpretation of the data. Errors are reviewed with the examiner and their site principal investigator ([name], [name], or [name]). If the assessment is failed, the examiner practices at least 1 more time and submits a new certification video for review; this process can continue until the examiner passes certification. After initial certification, the examiner can begin testing study participants and is required to video record the first testing session with a person with MS; this video is also reviewed for consistency with study protocol, and feedback shared with the examiner. To ensure continued adherence to testing protocol, examiners record the laboratory visit for every 10th session, and this recording is reviewed by investigators as with the earlier certification videos. Consent for video recording is included in the study consent form.

### Multisite Coordination

To ensure multisite coordination and fidelity of procedures, the full study team, including all examiners and investigators at all study sites, met weekly to discuss study-related questions and troubleshoot any issues that had arisen during the prior week for the first 18 months of the study. As fewer questions arose, and study teams were immersed in recruitment and testing, meetings were shifted to every other week (months 18-36). After month 36, meetings were shifted to once per month. UM keeps a record of all meeting agendas and meeting minutes, and any clarifications to the study manual of procedures are recorded by the UM team and updated in a shared folder that includes all study-related documents.

UM serves as the data coordinating center for the study. Data from all sites are fully accessible to the investigators and staff at UM, who conduct monthly data checks to assess for data completeness and quality. Data double entry of case report forms from each study site and data cleaning, scoring, and merging to produce final, analyzable datasets are completed by UM staff and investigators.

### Sample Size Analyses

We conducted analyses to determine the sample size needed to address all study aims. The goal of the first study aim is to determine whether the ambulatory tests are able to detect cognitive decline from baseline (T1) to 1-year (T2) or 2-year follow-up (T3) for individuals where clinic-based tests do not detect decline. The proportion of participants who show no decline or improvement, absolute but subtle decline (change <1/2 SD), meaningful decline (change between 1/2 SD-1 SD) [71], or clinically significant decline (≥1 SD decline) [71,72] will be calculated for both ambulatory and clinic-based neurocognitive tests. For each cognitive domain, a binary variable will be created for each participant indicating whether the ambulatory and clinic-based cognitive measures are consistent with each other (eg, agree) about the degree of change or laboratory-based or ambulatory measures indicate a larger degree of decline. We will test whether the proportion of cases where ambulatory measures indicated a larger degree of decline (relative to clinic-based tests) is statistically different from 0; sample size analyses for this test indicate that a sample of 199 will have 95% power (with critical α=.01) to detect significance, where ambulatory cognitive tests show a greater level of decline compared to clinic-based tests in as few as 1.5% (n=3) of cases. This suggests that our expected final sample size of 210 has the power to detect even modest differences in analyses comparing proportions of the sample that show a decline on ambulatory cognitive tests but not on clinic-based tests.

Effects sizes from a prior study of perceived cognitive functioning in daily life in MS [73-75] informed sample size estimation for the second and third aims, which examines factors that predict later cognitive decline or that are predicted by cognitive changes. We calculated the sample size needed to test the aims in a linear regression framework [76], which is a relatively conservative estimate, given that the repeated measures design imparts greater measurement reliability and therefore greater power [77]. We based our estimates on models that included up to 6 covariates (see list of covariates below) and 6 predictor variables of interest (eg, sleep quality, physical activity, pain, fatigue, mood, and stress) in predicting any given cognitive variable. The sample size for these models was expected to provide a conservative estimate for power required for the third aim (which had fewer predictors in each model). Critical α (*P*) value was set at .01. Our analyses indicated that a sample size of 214 will have 95% power (critical *t*=2.34, 1-sided significance test) to detect an association between cognitive functioning, and the variable expected to show the weakest association with cognition: mood (effect size *f*^2^=0.075).

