#### Specific Aim 1: Are Ambulatory Measures of Subjective and Objective Cognitive Function More Sensitive to Longitudinal Changes in Cognitive Function Compared With Conventional Clinic-Based Assessments?

Nonparametric tests (Wilcoxon signed rank test, 2-tailed) will be used to compare cognitive test scores (ambulatory vs clinic-based measures) for each participant at each time point. We will test whether the proportion of cases where the ambulatory test indicates a greater degree of cognitive decline compared to the clinic-based cognitive tests is statistically different from 0. Additional sensitivity tests of the paired differences in proportions of 4 categories (no decline, absolute but subtle decline, meaningful decline, or clinically significant decline) for each cognitive domain between ambulatory and clinic-based neurocognitive tests at both 1- and 2-year follow-up will be conducted [80]. Mixed effects models will be used to examine changes over time for each cognitive measure, with the expectation that the ambulatory measures will show larger time effects at both 1- and 2-year follow-up.

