##### Long Term

In terms of distal prediction of social and physical function from ambulatory cognition, we will conduct MLMs with the cognitive variables (averaged across each time period) predicting social and physical functioning at 1- and 2-year follow-up. The change will be modeled within an analysis of covariance framework, where T2/T3 values for an outcome of interest are modeled controlling for T1 values of the said outcome. These MLMs exploring long-term associations between cognitive changes and changes in social and physical functioning will be repeated in a set of secondary analyses with standard clinic-based cognitive test scores as predictor variables. Prediction of long-term changes in social and physical functioning from ambulatory cognitive measures will be compared to the ability of laboratory-based measures to predict these same changes. Ambulatory measures of cognition are of primary interest for specific aim 3, given that their microlongitudinal burst design allows for examination of short- and long-term associations, and are assumed to be more reliable and therefore more likely to demonstrate robust associations with the other functional outcomes.

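### Aim 1 grades decline with the same unspecified-SD bands on both instruments and no allowance for measurement error, so grade differences mix reliability with sensitivity, in no fixed direction

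*Protocol article*

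**What the plan says.** The Sample Size Analyses section sets four grades of change. The lower two are "no decline or improvement, absolute but subtle decline (change <1/2 SD" and the upper two are "meaningful decline (change between 1/2 SD-1 SD) [71], or clinically significant decline (≥1 SD decline". They "will be calculated for both ambulatory and clinic-based neurocognitive tests", so one set of bands serves both instruments. The SD is not identified as baseline, normative or change-score, and the grading rule contains no correction for reliability or practice.

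The grades feed two analyses. The main Aim 1 test asks whether "the proportion of cases where ambulatory measures indicated a larger degree of decline (relative to clinic-based tests) is statistically different from 0". Aim 1 was sized on it: "a sample of 199 will have 95% power (with critical α=.01"), for a proportion of 1.5%, or 3 cases. The Specific Aim 1 section adds "sensitivity tests of the paired differences in proportions of 4 categories" at both follow-ups. It also plans mixed models of change for each measure, which use no bands.

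On reliability, the Long Term part of Specific Aim 3 says that the ambulatory measures "are assumed to be more reliable and therefore more likely to demonstrate robust associations with the other functional outcomes". No coefficient is given for either instrument.

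**The concern.** Hypothesis 1 is about sensitivity to true change. An observed change is true change plus the error of two occasions, and the error part depends on retest reliability. With one fixed band for both instruments, the chance of being graded a decliner without having declined differs between them whenever their reliabilities differ. The plan expects such a difference: a burst holds up to 4 × 14 = 56 sessions, against one laboratory visit.

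A gap in graded decline could then come from better detection, from more noise, or from both, and the planned comparison cannot separate them. At stake is the headline claim of Aim 1. The paired comparison of the grades could hide or reverse a real advantage of the ambulatory tests, and the test against 0 could announce one that does not exist.

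**Working it through.** **The plan's own figure.** The probability of seeing at least one case among 199 at a true proportion of 1.5% is 1 − 0.985^199 = 0.951, and ln 0.05 / ln 0.985 = 198.2, which rounds up to 199. The expected count is 0.015 × 199 = 3.0. So the stated size is the n that gives a 95% chance of at least one such case. It contains no term for measurement error.

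**Inputs.** From the protocol: cut-offs at 0, 1/2 and 1 SD, the same for both instruments, and an expected final sample of 210. Assumed, because the protocol gives no figures: burst reliability 0.95, clinic reliability 0.70 to 0.90, normal errors independent between visits and between instruments, no practice effect. Steps 1 to 3 take the SD as the baseline SD.

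**Step 1: no true change.** In baseline SDs, the SD of change is s = √(2(1 − r)), and P(decline of at least c) = Φ(−c/s).

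| Instrument, r | s | at least 1/2 SD | at least 1 SD |
|---|---|---|---|
| Burst 0.95 | 0.316 | 5.7% | 0.1% |
| Clinic 0.90 | 0.447 | 13.2% | 1.3% |
| Clinic 0.80 | 0.632 | 21.5% | 5.7% |
| Clinic 0.75 | 0.707 | 24.0% | 7.9% |
| Clinic 0.70 | 0.775 | 25.9% | 9.8% |

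The noisier test shows more decline in both upper grades, though nobody has declined.

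**Step 2: one grade against the other, no true change.** With clinic r = 0.80 the four grades hold 50.0, 44.3, 5.6 and 0.1% (burst) and 50.0, 28.5, 15.8 and 5.7% (clinic). Ambulatory worse = 0.443 × 0.500 + 0.056 × 0.785 + 0.001 × 0.943 = 26.6%. Clinic worse, by the same sum, is 34.8%. Over clinic r from 0.90 to 0.70, ambulatory worse is 27.1% to 26.4% and clinic worse is 30.9% to 37.0%. So a two-way comparison leans towards the clinic test, while the one-way test sees about 55 to 57 of 210 cases against a null of 0.

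**Step 3: a true decline of 0.2 SD in everyone.** P(decline of at least c) = Φ((0.2 − c)/s). At 1/2 SD this gives 17.1% for the burst and 25.1% (r = 0.90) to 34.9% (r = 0.70) for the clinic, so the noisier test still looks more sensitive. For any decline (c = 0) it gives 73.6% against 67.3% to 60.2%, so the more reliable test looks more sensitive. The same data point in opposite directions at different grades.

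**Step 4: the SD read as the SD of change.** With no true change, both instruments give Φ(−0.5) = 30.9% and Φ(−1) = 15.9%, and the asymmetry is gone. With the 0.2 SD decline, the 1/2 SD grade becomes Φ(0.2/s − 0.5): 55.3% for the burst against 47.9% (r = 0.90) to 40.5% (r = 0.70) for the clinic. The order of Step 3 is reversed. Ambulatory worse is 33% with no true change, so the test against 0 is still met by error.

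**Step 5: reliable-change flags.** Flag a change beyond 1.645 standard errors of difference, which is 5% one-sided for each measure. With no true change, ambulatory-only = clinic-only = 0.05 × 0.95 = 4.75%. With a 0.5 SD decline in everyone, P(flag) = Φ(0.5/s − 1.645): 47% for the burst and 30% (r = 0.90) to 16% (r = 0.70) for the clinic. Ambulatory-only is then 33% to 40% and clinic-only 16% to 8%. The paired contrast is balanced when nothing changes and follows precision when something does.

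**The case against.** A reader might infer that the bands are simply biased against the burst measure. The documents do not support that. The main test counts only cases with a worse ambulatory grade, so error in either instrument pushes it towards the ambulatory tests. The any-decline grade also favours the more reliable test once there is true decline. The direction in the upper grades depends on an SD that the protocol does not define. That the burst is the less noisy measure is the protocol's assumption, without a coefficient; if the reliabilities were swapped, the no-change asymmetry would swap too. Nor should a uniform decline of exactly 1/2 SD be used as an illustration: the bands are symmetric about that value, so the two instruments tie at every pair of reliabilities.

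Three further points deserve weight. First, the size depends on assumed reliabilities, and at 0.95 against 0.90 the no-change gap is modest (30.9% clinic worse, 27.1% ambulatory worse). Second, the mixed models are free of cut-offs and give a separate view of change; but they do not replace the graded endpoint on which Aim 1 was sized. Third, the bands rest on cited sources, and the exact SD could be left to an analysis plan. That excuses the missing definition of the SD more than the rule itself: the protocol states the bands, their common use and the test against 0, and no choice of SD makes that test robust to error.

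**Conclusion.** The point holds in this form: common bands in an unspecified SD, with no allowance for error, make the Aim 1 grade comparison a mixture of reliability and sensitivity. With baseline-SD scaling and assumed reliabilities of 0.95 and 0.70 to 0.90, error alone produces a decline of at least 1/2 SD in 6% against 13-26%, and of at least 1 SD in 0.1% against 1-10%. That favours the noisier test in a paired comparison of those grades. The direction is not general: it changes with the grade, with the SD chosen, with the amount of true decline and with the test used. The test against 0 is met by error alone, at about 26-27% in the same setting. The mechanism needs only unequal reliabilities, which the protocol itself expects; the percentages rest on the assumptions listed. The plan should be changed, and the Results section states that data analysis had not started.

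**What to change.** 1. State which SD defines the bands and from which sample it comes.
2. For each measure, define decline by a reliable change index: practice-corrected change divided by that measure's standard error of difference, with the same one-sided false-positive rate throughout.
3. Base the Aim 1 comparison on a paired test of ambulatory-only against clinic-only flags (McNemar type), in place of the test against 0. Both changes are needed: adjusting for reliability alone leaves the test against 0 satisfied by error, and a paired test on the present bands still compares instruments with unequal false-positive rates.
4. Keep the four SD bands as a descriptive table.

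The change is to analysis wording only; data collection is unaffected. The cost is that a reliability or error estimate, and a practice correction, must be fixed in advance for each clinic test. The ambulatory error can be estimated from session or split-half variance within the burst. That leaves out fluctuation between bursts and so may be too small, which calls for a sensitivity range. The sample size statement for Aim 1 would need to be redone for the paired test.

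### The Aim 1 case rule counts people whose clinic test also declined, although the stated goal and the power conclusion concern only decline that the clinic tests did not detect

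*Protocol article*

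**What the plan says.** The Sample Size Analyses section opens by giving the goal of Aim 1 as detecting decline with ambulatory tests "for individuals where clinic-based tests do not detect decline". It then grades change on each type of test in four levels. The lowest two are set by "The proportion of participants who show no decline or improvement, absolute but subtle decline (change <1/2 SD"), the third runs from 1/2 SD to 1 SD, and the last is "or clinically significant decline (≥1 SD decline"). For each cognitive domain a variable described as binary records whether the two measures "are consistent with each other (eg, agree) about the degree of change or laboratory-based or ambulatory measures indicate a larger degree of decline".

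The quantity to be tested against 0 is "the proportion of cases where ambulatory measures indicated a larger degree of decline (relative to clinic-based tests"). The power statement (199 participants, 95% power, α = .01, 1.5% or 3 cases) is attached to that event. The closing sentence then says that the expected 210 participants give power for analyses "comparing proportions of the sample that show a decline on ambulatory cognitive tests but not on clinic-based tests".

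Specific Aim 1 in the Data Analysis section tests "the proportion of cases where the ambulatory test indicates a greater degree of cognitive decline compared to the clinic-based cognitive tests". It too sets no condition on the clinic grade.

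**The concern.** The goal and the closing power sentence describe one event, and the test between them uses another. A participant whose clinic score falls by 0.6 SD and whose ambulatory score falls by 1.1 SD is a case under the rule. Yet the protocol's own label for that clinic result is meaningful decline, so the clinic test did not miss it.

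At stake is the meaning of the Aim 1 proportion. If it is read as the section's goal and closing sentence invite, as decline found by ambulatory tests but not by clinic tests, it will include people whom the clinic tests also graded as declining, and it will overstate what ambulatory testing adds. The power statement has the same problem: it is worked out for the broader event and then claimed for the narrower one.

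**Working it through.** **1. The plan's own figure.** Inputs from Sample Size Analyses: proportion 1.5%, null 0, N = 199, power 95%. Against a null of exactly 0 any single case rejects, so power is P(at least one case) = 1 − (1 − 0.015)^N.

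- N = 199: 1 − 0.985^199 = 0.9506.
- Required N: ln 0.05 / ln 0.985 = 198.2, rounded up to 199.

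The figure reproduces, so this is not an arithmetic error. It belongs to whichever event has a 1.5% probability, and in the text that is the larger-degree event.

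**2. Which grade pairs count.** With four grades per test there are 4 × 4 = 16 pairs. The ambulatory grade exceeds the clinic grade in six:

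| Clinic grade | Ambulatory grade | Counted | Clinic test also declined? |
|---|---|---|---|
| none | subtle | yes | no |
| none | meaningful | yes | no |
| none | clinically significant | yes | no |
| subtle | meaningful | yes | yes |
| subtle | clinically significant | yes | yes |
| meaningful | clinically significant | yes | yes |

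The tested event strictly contains the target event. This needs no assumption beyond the protocol's labels.

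**3. Does another cut-off for detecting decline remove the mismatch?** The text states none. At 1/2 SD, the meaningful–significant pair is still counted although the clinic test detected decline. At 1 SD, no counted pair has clinic-detected decline, but the rule then counts pairs in which neither test detected decline (for example none–subtle). Rule and goal differ under every cut-off.

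**4. Illustrative size.** The documents give neither reliabilities nor expected change, so everything here is assumed. Let true decline be the same on both tests, Normal with mean 0.1 and SD 0.2 in baseline-SD units. Observed decline adds independent error with variance 2(1 − r), where r = 0.80 for clinic and 0.90 for ambulatory tests.

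- Clinic variance: 0.04 + 0.40 = 0.44. Ambulatory variance: 0.04 + 0.20 = 0.24. Covariance: 0.04.
- No clinic decline, ambulatory subtle 15.9%, meaningful 6.6%, significant 1.1%: total 23.7% after rounding.
- Clinic also declined: 5.1% + 1.0% + 0.8% = 6.9%.
- Counted: 30.5%. Ratio: 30.5 / 23.7 = 1.29. Of 210 participants, about 64 are counted and about 50 have missed decline.

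The grid crossed clinic r 0.7, 0.8, 0.9 with ambulatory r 0.8, 0.9, 0.95 and (mean, SD) of (0, 0), (0.1, 0.2), (0.2, 0.3). The ratio runs from about 1.05 (26.4% vs 25.0%) to 1.87 (34.1% vs 18.3%). Cases in whom the clinic test also declined are 5% to 46% of those counted, or about 3 to 33 of 210.

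A second assumed model gives both tests the same mean decline (0 to 0.5 SD), the same SD of change (0.3 to 1.0) and a correlation of 0 to 0.9. That share then runs from about 8% to 85%.

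**5. Power for the narrower event.** If 1.5% is the larger-degree proportion and only a share of it is missed decline (the share is an assumption):

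| Share | p | Power at 199 | Power at 210 | N for 95% |
|---|---|---|---|---|
| 100% | 1.5% | 95.1% | 95.8% | 199 |
| 75% | 1.125% | 89.5% | 90.7% | 265 |
| 50% | 0.75% | 77.6% | 79.4% | 398 |
| 25% | 0.375% | 52.7% | 54.6% | 798 |

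**The case against.** The strongest reply is that the broader rule suits the hypothesis. Hypothesis 1 in the Introduction, the Specific Aim 1 heading and the Discussion all speak of greater sensitivity to change, and a larger ambulatory decline is a direct reading of that, whatever the clinic grade. This stands. It is why the broader proportion should be kept, and why one cannot say that hypothesis 1 goes unmeasured. Rewording the goal and closing sentence would also restore consistency, but it would leave the stated goal without a measure.

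Specific Aim 1 also plans paired comparisons of all four categories and mixed models, so the aim does not rest on one figure. That is so, but the category comparisons are labelled sensitivity tests and do not redefine the case. Nor would the planned test decision be likely to change: against a null of 0 one case is enough.

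A reader might infer more than the documents support, in two ways:

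- **That only ambulatory decline of at least 1/2 SD should count as missed decline.** This would make the rule overstate it about fourfold in the base case (30.5% against 7.7%). The protocol labels smaller losses as decline, and the Introduction names subtle decline as a target. The 1/2 SD floor is not the protocol's. A pair such as +0.02 and −0.02 SD shows the weakness of a cut at zero, but it fits the goal as worded.
- **That the binary variable pools laboratory-larger with ambulatory-larger participants.** The next sentence, and Specific Aim 1, name ambulatory-larger alone as the tested proportion ("the ambulatory test indicates a greater degree of cognitive decline compared to the clinic-based cognitive tests is statistically different from 0"), so no planned test uses the pooled share. What remains is a variable called binary that lists three outcomes.

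**Conclusion.** The point holds as a mismatch between the tested event and the goal and power conclusion stated in the same section. Three of the six counted grade pairs are people whose clinic test also declined, so the proportion cannot be smaller than the missed-decline proportion and will exceed it whenever any such person is in the sample. That follows from the protocol's grades alone.

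The size is not determined by the documents. It is about 1.3 times in the base case and about 1.05 to 1.87 times over the grid, assuming the same true decline on both tests, independent errors and the stated reliabilities. A different assumed model gives a wider spread. The N of 199 is correct for a 1.5% event, and its transfer to missed decline is valid only if 1.5% is meant as the missed-decline proportion. This should be corrected before analysis; it affects what is reported and claimed, not the data.

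**What to change.** In Sample Size Analyses and Specific Aim 1:

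1. For the stated goal, derive the case from the cross-table of grades: clinic grade in the lowest category (no decline or improvement) and any ambulatory decline grade, with subtle, meaningful and clinically significant shown separately. Derive the mirror case (clinic decline, no ambulatory decline) in the same way.
2. Keep the larger-degree proportion as a separately labelled measure of the broader sensitivity hypothesis, and word each conclusion to match its own definition.
3. Code the agreement variable with three levels: ambulatory larger, agree, laboratory larger.
4. State that N = 199 with 95% power applies to the larger-degree event, unless 1.5% is restated as the missed-decline proportion.

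The cost is a change of wording and a recoding of grades already planned, with no new data. The Results section says analysis had not started at submission. The downside is a lower headline proportion and slightly more tabulation.
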